Many children with asthma can achieve symptom and disease control by using inhaled corticosteroid (ICS) therapy combined with a long acting B_2_ agonist (LABA) and/or a leukotriene receptor antagonist(LTRA) (International ERS/ATS guideline, 2014). However, a number of children with asthma experience frequent symptoms despite being prescribed high dose ICS (Nagakumar and Thomas, 2013; Hedlin *et al.*, 2014)**.**

Drug delivery by inhalation of various medications is the most common treatment approach for asthma in all patient populations. Inhalation therapy offers rapid onset and improved efficacy compared to systemic drug delivery (Bisgaard, 1997).While ICS therapy is well accepted as the foundation of optimal therapy for most asthma patients, efficacy of the therapy depends on drug being delivered correctly into the lungs and taken on a regular basis as a preventer therapy(Machira *et al*., 2011).

It has been suggested that good inhaler technique is an essential aspect of optimal asthma management. Education on inhaler technique has been shown to improve self- management and adherence to asthma therapy. Evidence is available demonstrating that asthma outcomes correlate with proper inhaler technique and that periodically assessing this treatment aspect has a positive impact on asthma control(Bryant *et al*.,2013; AL-Jahdali *et al*., 2013). Moreover, early and repeated tailored education and follow-up assessment can result in sustained good inhaler technique (Klot *et al*., 2011).However, many asthma clinics treating children are unable to effectively evaluate these important patient treatment variables.

Adherence to pharmacotherapy is also considered an important basic tenet of asthma management. Adherence can simply be defined as the extent to which a patient follows the instructions of the prescriber (Osterberg and Blaschke, 2005).While inhaled therapy technique is an essential feature of asthma pharmacotherapy, some patients with good technique may have poor inhaler adherence. Available data suggest the average medication adherence to ICS in children is only approximately 50% (Fish *et al*., 2001; Osterberg and Blaschke, 2005).

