**Study design**

A randomised intervention trial will be used. Participants will be randomised to either an immediate (I-med) or a delayed (D-med) mobile technology DOT intervention. Randomisation will be restricted based on two factors including age (categorized as Young Children ages 2 up to 5 years, Children ages 5 up to 12 years and Young People ages 12 up to and including 16 years) and patient gender (Gore, 1981).

Both subject groups will receive standard-of-practice asthma education and management in the Asthma Clinic prior to study enrolment. Participants allocated to the I-med group will take part in the mobile technology DOT intervention for the first 6 weeks. Outcomes will be evaluated at the start (week 0) and end of the 6 week intervention period and during clinic visits at weeks 12 and 18 for follow-up. Those participants allocated to the D-med group will have the DOT intervention started after a 6 week “intervention-free” interval with usual Asthma Clinic care. Outcomes in the D-med group will be assessed at baseline (week 0), week 6 (intervention start), week 12 (end of intervention), and at weeks 18 and 24 for follow-up. (see Figure 1)

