**Intervention**

**Intervention and data collection**

The project will utilise a simple application (app)set up on each participant’s or parent/guardian’s mobile smartphone, tablet, or other device that will allow video capture and transmission of ICS inhaler administration. Before the study intervention period is initiated in a given subject, the participant and/or parents/guardians will be trained in use of the video DOT application and how to upload the videos to a web-based repository. As a general rule, it would be expected that young people greater than 12 years of age will record and upload the video themselves, while parent/guardian assistance will be needed for younger children. All mobile devices will be tested after installation to make sure the Dropbox®([https://www.**dropbox**.com](https://www.dropbox.com))repository connection is active and ready to use.

Usual asthma care for the participant will be adopted throughout the study. Regarding the inhaler use, children aged 5 years or older may administer the medication themselves while a parent/guardian will be responsible for inhaler administration in patients 2 up to 5 years of age. However, parent/guardian administration will be allowed if that is usual asthma care in any age child.

Patients who are enrolled in the study will be randomised into two groups (I-med or D-med) as previously described. Participants or parents/guardians of participants will be asked to capture a DOT video twice daily (morning and evening) on their mobile devices of ICS use by the patient. It will be requested that morning videos occur before 9am on school days and before 11am on weekends and holidays, and evening videos occur between the evening meal and bedtime. In the I-med group, participants will be asked to upload daily video recordings via the internet to a repository for a 6 week period at the start of the study. Participants in the D-med group will be free from DOT for the first 6 weeks of the study and will be asked to carry out their usual therapy management. After that, DOT as described above will be applied for the next 6 weeks.

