**At study end (both groups)**

- GP prescribing records for the 12 months leading up to, and during the study time period
- Community pharmacy dispensing records for the 12 months leading up to, and during the study time period

Clinician assessment of participant asthma severity will be defined according to accepted guidelines and asthma control will be categorized as uncontrolled, partially controlled, or controlled (BMT/SIGN 2012). Data regarding the medication profile will include any respiratory or allergy drugs added or removed, existing drug dosage changes, and drugs initiated for respiratory infections.

Patient inhaler technique will be evaluated by reviewing each video from the first 2 days of the intervention period and then a sample (at least one weekly) of the videos that have been uploaded to the repository application. The presence/absence of every required video will be documented.

Inhaler technique will be assessed and categorized on a three-point scale as effective, partially effective or poor (Patterson *et al.*, 2005). Inhaler technique evaluation will be based on criteria relevant to the child’s inhaler manufacturer administration directions, such as removal of cover, priming of device, vigorous shaking before each actuation, respiratory expiration before actuation, and holding of breath after inspiration. Effective technique will be recorded when the participant meets all relevant criteria. Partially effective technique will be recorded when errors in technique are observed but it is thought that the participant would receive some medication. Poor inhaler technique will be recorded when critical errors in technique occur such that it is considered unlikely that any medication would be inhaled (Patterson *et al.*, 2005; Melani *et al.*, 2011).

Adherence will be calculated based on total number of videos submitted during the 6 week intervention divided by the number of days during which DOT monitoring has occurred.

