**Outcomes measure**

The primary outcome measures in this pilot study concern two areas. Firstly, the feasibility, practicality, and persistence of using a mobile DOT approach in the management of asthma in children and young people will be assessed by evaluation of ICS inhaler technique and monitoring inhaler use adherence. Secondly, asthma control associated with the mobile DOT approach will be assessed with clinical (including number of patients who progress to controlled category) and laboratory disease assessment, participant-reported medication adherence, and quality of life measurements (PAQOLQ/PACQOLQ and ACT/C-ACT).

Secondary outcome measures for the study include any impact of mobile DOT on participants’ inhaler technique and adherence. These two aspects of asthma management will be assessed by comparisons between intervention groups and within groups during, and across, phases of the study. Participant and parent/guardian factors that influence the impact of the DOT method on inhaler use and adherence also will be determined.

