**Data analysis**

Statistical analyses will be conducted by the researcher after entering all data into SPSS (IBM SPSSv.23, USA). All nominal data collected during the study will be analysed using descriptive approaches. Group differences (I-med and D-med groups) will be studied using the independent sample Student t-test. If the data are not normally distributed non-parametric statistics will be utilised (Mann-Whitney U test for independent group differences). A paired Student t-test will be used to detect any differences associated with the study periods within each group

Adherence to ICS use in participants will be determined based on the patients’ general practitioner records of medicine prescribed and the patients’ records of medicine dispensed within the 6 week period, monitoring of video submissions, as well as the total scores achieved from the MARS questionnaires.

Categorical variables associated with non-adherence will be analysed using Chi-squared analysis. If the expected frequency falls below 5, the Fisher’s exact test will be employed.

Factors that affect the adherence to ICS inhaler use will be determined using patient demographic and clinical data together with responses obtained through administration of BMQ, CES-D, MARS, PACQOLQ/PAQOLOQ and ACT/C-ACT questionnaires to the participants and participants’ parents/guardians as appropriate. Multiple regression analysis will be performed to evaluate the relative contribution of different predictors to non-adherence.

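### Records-based ICS adherence is tied to an unidentified 6-week window, too short for refill data at child level, while the 12 months of records collected have no stated use

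*Protocol*

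**What the plan says.** The Data analysis section of the Protocol derives ICS adherence from GP prescribing records, "records of medicine dispensed within the 6 week period", video submissions and MARS totals. It gives no formula for the records and does not identify the six weeks.

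The list of data gathered at study end is much wider: "GP prescribing records for the 12 months leading up to, and during the study time period" and "Community pharmacy dispensing records for the 12 months leading up to, and during the study time period". No section assigns a use to the months outside the six weeks. Objective 2, under Aims and objectives, names pharmacy and GP records as an adherence source and sets no window.

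Under Study design, the immediate (I-med) arm is seen at weeks 0 and 6 and "during clinic visits at weeks 12 and 18 for follow-up". The delayed (D-med) arm has a DOT-free period in weeks 0-6 and DOT in weeks 6-12, and is then assessed "at weeks 18 and 24 for follow-up". The Outcomes measure section plans to examine adherence through "comparisons between intervention groups and within groups during, and across, phases of the study".

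**The concern.** A dispensing record shows when an inhaler was collected, not when it was used. It becomes a measure of adherence only over a period that is long relative to the time between collections. Over 42 days most children will collect no inhaler, one or two, so a fill count mainly reflects where the window falls in the refill cycle.

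Two uses are at stake.

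- **Randomised contrast.** Weeks 0-6 are the only DOT versus no-DOT comparison between arms. D-med submits no videos then and MARS is self-reported, so the prescribing and dispensing records are the only adherence source in both arms that does not rest on self-report. If the six weeks instead mean each arm's DOT period (weeks 0-6 in I-med, 6-12 in D-med), the records give no such contrast at all.
- **Factors behind non-adherence.** Data analysis plans chi-squared tests and multiple regression on non-adherence. These need a usable value for each child.

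**Working it through.** The plan states no figure that depends on this window, so there is none to reproduce. The check asks how much a child's value varies through refill timing alone.

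**Inputs**

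- Window W: 42 days (Data analysis), compared with 365 days (records collected at study end).
- True adherence a: 50%, the average given in Background; 90% is an assumed good adherer.
- Days of supply per inhaler at full use, S: not in the Protocol. Assumed 28, 30 or 60 days.
- Model: one inhaler per fill, refilled every T = S/a days, with the window starting at a random point in the cycle. Measured adherence = fills × S / W, uncapped.

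**Six weeks, a = 50%.** Here T = 56, 60 or 120 days, all longer than 42, so there is either no fill or one. P(one fill) = p = 42/T, and SD = (S/42) × √(p(1−p)).

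| S | p | P(no fill) | Value if one fill | SD (points) |
|---|---|---|---|---|
| 28 | 0.75 | 25% | 66.7% | 66.7 × √(0.75 × 0.25) = 28.9 |
| 30 | 0.70 | 30% | 71.4% | 71.4 × √(0.70 × 0.30) = 32.7 |
| 60 | 0.35 | 65% | 142.9% | 142.9 × √(0.35 × 0.65) = 68.1 |

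The mean is p × S/42 = 50% in every row, so the uncapped count is unbiased. A 100% cap applied at six weeks would change that: for S = 60 the mean becomes 0.35 × 100 = 35%.

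**Twelve months, a = 50%.** Expected fills are 365/T = 6.518, 6.083 and 3.042. With f the fractional part, SD = (S/365) × √(f(1−f)):

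- S = 28: 7.67 × √(0.518 × 0.482) = 3.8 points
- S = 30: 8.22 × √(0.083 × 0.917) = 2.3 points
- S = 60: 16.44 × √(0.042 × 0.958) = 3.3 points

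These depend on how close 365 is to a whole number of refill intervals. The ceiling is half a fill, 0.5 × S/365 = 3.8, 4.1 and 8.2 points, against 0.5 × S/42 = 33, 36 and 71 points over six weeks.

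**Telling children apart.** At a = 90%, T = 31.1, 33.3 or 66.7 days. The chance that a 50% adherer scores strictly below a 90% adherer over 42 days is:

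- S = 28: 0.25 + 0.75 × 0.35 = 51%
- S = 30: 0.30 + 0.70 × 0.26 = 48%
- S = 60: 0.65 × 0.63 = 41%

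Most of the rest are ties; for S = 60 the order is reversed in 0.35 × 0.37 = 13%. Over 365 days the ranking is correct in about 100% of pairs. With a wider assumed range of 25 to 100 days, correct ranking over six weeks is 59% down to 30%, and the 12-month SD is 2 to 12 points.

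**Group comparison.** With 36 per group and both groups near 50%, refill timing alone gives a standard error of SD × √(2/36) = 6.8, 7.7 or 16 points. At 80% power and two-sided 5% (multiplier 2.80), the smallest detectable difference is about 19, 22 or 45 points, before any real variation between children.

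**Days covered over 42 days, earlier supply carried forward, a = 50%.** Cover alternates S days on and S days off. For S = 60, 18/120 = 15% of such children are never covered in the window, 15% are always covered, and the rest are spread evenly, so SD = √(0.15 + 0.70/3 − 0.25) = 36.5 points. The same argument gives 13.6 for S = 28 and 16.6 for S = 30. This roughly halves the noise and leaves about 14 to 37 points per child.

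**The case against.** The strongest reply is that the Protocol fixes less than this criticism needs. It gives no scoring formula, combines records with videos and MARS, and does not say the window is exclusive. Six weeks plausibly mirrors the video period. Formula and carry-over handling are commonly left to a SAP, which is not at hand. Pack size, one inhaler per fill and regular refills are all assumed.

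Much of this stands, and it rules out three stronger readings that a reader might infer:

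- *That analysts are barred from the longer record.* Nothing prohibits it, and Objective 2 sets no window. What can be said is that six weeks is the only window stated and the other months have no stated use.
- *That a child supplied just before week 0 will be scored 0%.* This would follow from a fill count without carry-over, but the Protocol does not prescribe that count.
- *That the measure is biased and will conceal a DOT effect.* Under the model the uncapped group mean is right. The loss is of precision.

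What does not stand is treating the matter as detail deferred to a SAP. The six-week window is written into the Protocol and sits badly with the records requested and the cross-phase comparisons planned. The assumed supply range does not rescue it either: the coarseness appears throughout 28 to 60 days, and also at 25 and 100.

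**Conclusion.** The point holds as a badly chosen and unclear window for one component of adherence. At 50% adherence and an assumed 28 to 60 days per inhaler, a six-week fill count shows nothing dispensed for 25% to 65% of children and carries a refill-timing SD of about 29 to 68 points. Twelve months brings this to about 2 to 4 points. The harm is lost precision between groups and misclassification of individual children in the factors analysis. Video and MARS measures, and the primary outcomes built on them, are untouched. The figures rest on the assumed pack range and the regular-refill model; the direction does not depend on the exact pack size within that range. The gain to 2 to 4 points applies to a 12-month baseline measure only. No handling of 42 days of dispensing data can give that precision for weeks 0-6.

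**What to change.** Amend Data analysis so that it matches the records collected at study end:

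1. **Baseline and factors analysis.** Define records-based adherence as days supplied / days elapsed over the 12 months before enrolment only, capped at 100%, and use it for the analysis of factors behind non-adherence. Keep post-randomisation time out, because it includes DOT and differs by arm (18 versus 24 weeks).
2. **Study period.** Report it separately, over the same number of weeks in each arm (weeks 0-18 are available in both).
3. **Weeks 0-6 group comparison.** Use days covered, carrying forward supply dispensed before week 0, adjusted for the pre-enrolment 12-month ratio. Present it as supportive, since it stays imprecise (SD about 14 to 37 points per child at 50% adherence).
4. **Weeks.** State which weeks apply in each arm for every records-based figure.

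The cost is wording and some data handling, as the records are already requested. Days covered needs an assumption about unused stock. The pre-enrolment ratio describes adherence under usual care, so it does not answer which factors modify the response to DOT. This is a cheap improvement.

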**Aims and objectives**

The principal aim of this study is to evaluate the feasibility and clinical impact of a mobile DOT approach (via video capture in the patient’s home) on the administration technique for, and adherence to, ICS in children with partially controlled or uncontrolled asthma. A secondary aim is to determine factors that influence adherence to ICS in children with asthma.

The specific objectives are to:

1. Investigate the feasibility, practicality, and persistence of a mobile DOT technology approach in the home setting to assist with disease management of children and young people with partially controlled or uncontrolled asthma.
2. Assess inhaler technique and adherence to ICS therapy by use of DOT videos, parent/guardian and child self-report questionnaires (Medication Adherence Report Scale (MARS)), pharmacy records and patient’s general practitioner (GP) records.
3. Evaluate the impact of the DOT intervention on asthma clinical outcomes including physician assessment of disease control, medication changes, asthma control tests, health-related quality of life and pulmonary function studies in participating children.
4. Identify parental/guardian and patient factors that influence adherence to ICS in participating children and young people with asthma

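### Testing categorical factors against non-adherence by chi-squared or Fisher's exact test implies splitting numeric adherence measures, which loses power in those factor-by-factor tests

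*Protocol*

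**What the plan says.** The aim at issue is in the protocol's Aims and objectives: "A secondary aim is to determine factors that influence adherence to ICS in children with asthma". Objective 4 in the same section repeats it.

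Data analysis gives two tools for it. The first is a set of factor-by-factor tests: "Categorical variables associated with non-adherence will be analysed using Chi-squared analysis", with the rule "If the expected frequency falls below 5, the Fisher’s exact test will be employed". The second is a joint model: "Multiple regression analysis will be performed to evaluate the relative contribution of different predictors to non-adherence".

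The adherence measures are described in two places. Under Outcome measurements, At study end (both groups), the video measure is a ratio: "Adherence will be calculated based on total number of videos submitted during the 6 week intervention divided by the number of days" of monitoring. Data analysis adds GP prescribing and dispensing records for the 6-week period, and "monitoring of video submissions, as well as the total scores achieved from the MARS questionnaires". No categorical version of any of these is defined.

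**The concern.** A chi-squared or Fisher's exact test relates one categorical variable to another. Gender, household smoking or age band can supply one side. The other side has to be adherence, and every adherence measure in the protocol is a number or yields one. With two videos requested per day for 6 weeks, the video measure alone rests on up to 2 × 42 = 84 scheduled recordings per child. The named tests can run on such data only after each child has been put into an adherent or a non-adherent class.

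That step treats a child just below the cut like one who submitted almost nothing, and a child just above it like one who missed nothing. With at most 72 children, a real factor is then more likely to be reported as showing no association, and the answer depends on where the cut falls. The protocol gives no clinical or regulatory reason for working with two classes, and the same section already names the t-test and the Mann-Whitney test for other comparisons.

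**Working it through.** **The plan's own figures.** The protocol states no power for the factor analysis, so there is no figure to reproduce for it. Its only power calculation concerns quality of life (difference 1, SD 1.3, 80% power, 36 per group). Those inputs give 28 per group by t-test, and 36 per group has about 90% power. That is a separate matter. Only the total is used here: 36 + 36 = 72, with both groups receiving the intervention.

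**Assumptions, not in the protocol.** Adherence is normal with equal SDs. The factor has two levels, dividing the children 36/36 or 48/24. The overall share labelled non-adherent is q = 50%, 30% or 20%. Two-sided alpha is 0.05.

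**Step 1: numeric test.** t-test power follows from the noncentral t with 70 df and noncentrality d / √(1/n₁ + 1/n₂). Power of 80% needs:
- 36/36: d = 0.670, noncentrality 0.670 / 0.2357 = 2.84
- 48/24: d = 0.710, noncentrality 0.710 / 0.250 = 2.84

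**Step 2: the split.** With cut c, the non-adherent share at each factor level is Φ(c − μₖ), and c is chosen so that the weighted average is q. For 36/36 and q = 50%: Φ(0.335) = 0.631 and Φ(−0.335) = 0.369.

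**Step 3: power under the protocol's rule.** Sum the binomial probabilities of all 2×2 tables with p < 0.05, using uncorrected Pearson chi-squared, or Fisher's exact test when any expected count is below 5.

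Hand check for 36/36, q = 50%, by the normal approximation:
- difference 0.631 − 0.369 = 0.262
- null SE √(2 × 0.25/36) = 0.1179
- alternative SE √(2 × 0.631 × 0.369/36) = 0.1137
- (0.262 − 1.96 × 0.1179) / 0.1137 = 0.27, so power is about 61%, against 59.7% exactly

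Exact results when the t-test has 80% power. For 48/24 the two values are for the smaller level being the less adherent and the more adherent:

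| Factor | q = 50% | q = 30% | q = 20% | Points lost |
|---|---|---|---|---|
| 36/36 | 59.7% | 57.1% | 47.5% | 20-33 |
| 48/24 | 62.4% / 62.4% | 61.0% / 52.2% | 50.3% / 38.0% | 18-42 |

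The low values at q = 20% arise partly because the Fisher rule comes into play. In the level with 24 children the expected non-adherent count is 24 × 0.20 = 4.8.

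**Step 4: sensitivity to the effect.**
- Effect giving the t-test 90% power: 17-31 points lost for 36/36 and 15-42 for 48/24.
- d = 0.5, 36/36: t-test power 55%, loss 18-26 points.
- d = 0.3: t-test power only 22-24%, loss 5-12 points over both factor divisions.

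**Step 5: the rank alternative.** In simulation on normal data, with the effect set for 80% t-test power, Mann-Whitney keeps about 77-79%.

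**The case against.** Four points can be made for the plan.

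1. *The split is inferred.* No sentence says that adherence will be dichotomised, and how non-adherence is coded may be left to an analysis plan that is not shown. This stands as far as the cut-point goes: a reader might take its absence as a defect, but a protocol may leave it to the analysis plan. It does not remove the concern, because the loss comes from the tests that the protocol has already chosen and is present at every cut tried above.

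2. *The regression serves the aim.* This largely stands. Multiple regression ordinarily has a numeric outcome and can include categorical predictors. A reader might infer that the whole secondary aim loses this power. The document does not support that: the regression outcome is worded as non-adherence, but its scale is not stated. The loss is established for the factor-by-factor tests only.

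3. *The size is not a document figure.* This stands. Effect, factor division, cut and distribution are all assumed, and Step 4 shows how far the loss moves. No single range is a property of the plan.

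4. *Adherence may be bimodal.* This stands as a possibility. The protocol's Feedback questionnaires section foresees families who upload nothing or stop early. In one illustrative simulation with two clusters (20% against 50% in the low cluster, 36/36) and a cut between them, chi-squared had 74% power, the t-test 71% and Mann-Whitney 60%, so the split cost nothing. With the cut at 0.8 instead, chi-squared fell to about 32%. The cluster shapes are assumptions, so this shows only that the loss can disappear, and that this depends on a well-placed cut.

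**Conclusion.** The point holds for the factor-by-factor tests. The named tests do not fit the scale of the named adherence measures, and following the plan as written implies a split that discards information. With 72 children, roughly normal adherence, cuts at 20-50% non-adherent and an effect that the numeric t-test would detect with 80% power, the loss is about 20-33 points for a 36/36 factor and 18-42 points for a 48/24 factor. It shrinks with the effect and may be nil for clearly bimodal data.

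Nor should a reader infer harm to the trial's main results. The factor analysis is a secondary aim of a self-described pilot study, with no power claim attached to it. The primary outcomes and the comparisons between randomised groups do not rely on this step. The point is a worthwhile low-cost improvement, not a threat to the trial.

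**What to change.** In the protocol's Data analysis section, replace the chi-squared and Fisher sentences with wording such as:

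*Associations between categorical factors and adherence will be examined with adherence on its numeric scale (t-test or one-way ANOVA; Mann-Whitney or Kruskal-Wallis if not normally distributed). The same numeric measure will be the dependent variable of the multiple regression.*

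Any percentages of adherent and non-adherent children can stay as description.

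The cost is a short text change in one section, with no new data, visits or software. The downside is that a mean difference is slightly less simple to present than a percentage, and the percentage can still be shown beside it. If the video measure turns out clearly bimodal, the numeric tests may have no advantage over a well-placed cut.

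### MARS is named both as a measure of adherence and as a source of factors that explain adherence, so the planned regression can put the same construct on both sides

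*Protocol*

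**What the plan says.** All the wording at issue is in the protocol.

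- **MARS as a measure of adherence.** In Data analysis, adherence is to be determined from prescribing and dispensing records and from "monitoring of video submissions, as well as the total scores achieved from the MARS questionnaires". Objective 2 (Aims and objectives) likewise names MARS as a tool for assessing adherence, and Outcomes measure lists participant-reported adherence among the outcomes.
- **MARS as a source of explanatory factors.** Two paragraphs later in Data analysis: "Factors that affect the adherence to ICS inhaler use will be determined using patient demographic and clinical data together with responses" from a list of questionnaires, namely "responses obtained through administration of BMQ, CES-D, MARS, PACQOLQ/PAQOLOQ and ACT/C-ACT questionnaires".
- **The model.** The next sentence reads "Multiple regression analysis will be performed to evaluate the relative contribution of different predictors to non-adherence". It names no dependent variable, and the protocol gives no other list of predictors.
- **The aim served.** Objective 4 is to "Identify parental/guardian and patient factors that influence adherence to ICS in participating children and young people with asthma". It is separate from objective 2, which measures adherence.

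**The concern.** MARS is a self-report of adherence. It is not a belief, mood or circumstance that could bring non-adherence about. Listing it beside BMQ, CES-D, quality of life and asthma control as material for finding causes puts it in the wrong role.

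The harm takes two forms. If the outcome contains MARS, the MARS term partly explains itself and the model looks better than it is. If the outcome is video or dispensing adherence, MARS is a second reading of the same behaviour. Adjusting for it removes much of the association that the real candidates have with adherence. Either way, objective 4 could end with the finding that reported adherence goes with adherence, while beliefs and parental depressed mood appear unimportant.

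A smaller point of the same kind concerns the quality-of-life and asthma-control scores. They are on the list of factors, but Outcomes measure also treats them as outcomes of DOT. A score taken during or after DOT may be a consequence of adherence.

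**Working it through.** The protocol gives no figure to reproduce. The first check is which side of the model each item can sit on.

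**Step 1. Roles assigned by the text**

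| Item | Measure of adherence | Source of explanatory factors |
|---|---|---|
| Prescribing and dispensing records | yes | no |
| Video submissions | yes | no |
| MARS | yes | yes |
| BMQ, CES-D | no | yes |
| Quality of life, ACT/C-ACT | no (but outcomes of DOT) | yes |

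MARS is the only item in both columns.

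**Step 2. Timing, from Outcome measurements.** BMQ and CES-D are scheduled at baseline only, so they precede DOT in both groups. MARS, quality of life and ACT/C-ACT are repeated at every visit, so for these the choice of visit matters.

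**Step 3. Illustration of direction and size.** The inputs below are assumptions, not figures from the protocol. All variables are standardised. A true determinant correlates *b* = 0.4 with true adherence. MARS, video and dispensing each correlate *r* with true adherence, with independent errors. Then each measure correlates *br* with the determinant, and any two measures correlate *r*² with each other.

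*(a) Video outcome.* The coefficient of the determinant is *br* without MARS and *br*(1 − *r*²)/(1 − *b*²*r*²) with MARS. At *r* = 0.6: 0.24 without; 0.24 × 0.64/0.9424 = 0.163 with.

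*(b) Composite outcome (mean of the three measures, rescaled to unit variance).* The variance of the mean is *V* = (1 + 2*r*²)/3. The coefficient is *br*/√*V* without MARS, and that value times (1 − *V*)/(1 − *b*²*r*²) with MARS. At *r* = 0.6: *V* = 1.72/3 = 0.573; 0.24/0.757 = 0.317 without; 0.317 × 0.427/0.942 = 0.144 with.

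*(c) The same MARS score on both sides.* R² = 1 and every other coefficient is 0, by construction.

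Range over *r*, with *b* held at 0.4:

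| *r* | Video: without → with MARS | Share kept | Composite: without → with MARS | Share kept |
|---|---|---|---|---|
| 0.4 | 0.16 → 0.14 | 86% | 0.24 → 0.14 | 57% |
| 0.6 | 0.24 → 0.16 | 68% | 0.32 → 0.14 | 45% |
| 0.8 | 0.32 → 0.13 | 40% | 0.37 → 0.10 | 27% |

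**Step 4. Effect at the planned size.** A simulation of least-squares fits at *r* = 0.6 with 2 × 36 = 72 children (4,000 runs) agrees with the formulas:

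| Outcome | Coefficient, without → with MARS | Power for the determinant | Mean R² |
|---|---|---|---|
| Video | 0.24 → 0.17 | 0.54 → 0.30 | 0.07 → 0.18 |
| Composite | 0.32 → 0.14 | 0.78 → 0.44 | 0.11 → 0.60 |

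Fit improves while the chance of finding the real determinant falls.

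**The case against.** Several parts of the opposing case have force.

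- **No circular model is written down.** A reader might infer that the protocol puts MARS on both sides of one regression and that R² will be 1. The text does not support that. The dependent variable is not named, the predictors are not itemised in the regression sentence, and MARS may be on the list because it supplies the outcome. R² = 1 needs the same score on both sides, which nothing prescribes. This stands. But the list is introduced as the material for finding factors, and the sources of adherence had already been given, so MARS as a predictor remains the natural reading.
- **A statistical analysis plan may settle the model.** True for the dependent variable and the final covariates. It is not an answer to MARS being named in the wrong role, because a plan that follows the protocol inherits it.
- **MARS before DOT can be a legitimate covariate.** For later video adherence, the week 0 score is prior self-reported adherence, and adjusting for it answers a predictive question. This stands and is allowed for in the fix. It does not make MARS a factor that explains adherence.
- **Timing of quality of life and asthma control.** A reader might infer that the protocol plans to use values taken after DOT as predictors. It does not say so, and BMQ and CES-D are collected only at baseline. This is a clarification to add, not an error in the text.
- **Video adherence as the only outcome.** That would discard the planned multi-source assessment. Videos exist only during DOT, and a missing upload may be a technical failure. The concern gives no ground for that change or for altering the protocol's definition of video adherence.

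**Conclusion.** The concern holds in a limited form. The protocol assigns MARS two incompatible roles and places the second directly before the regression, so its wording permits a model in which adherence is explained by adherence. It does not prescribe one.

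The direction of harm is clear: inflated fit and masked determinants. The size is not fixed by the protocol. Under the assumed correlations, a real determinant keeps 40% to 86% of its coefficient when the outcome is video adherence, and 27% to 57% when the outcome is an equally weighted composite containing MARS. These figures rest on *b* = 0.4, *r* between 0.4 and 0.8, equal validity of the three measures and independent errors.

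The reach is also limited. Identifying factors is a secondary aim in what the protocol calls a pilot, and the comparison of the randomised groups is untouched. It should be corrected because objective 4 depends on it and the correction costs almost nothing.

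**What to change.** Amend the last part of Data analysis:

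1. Remove MARS from the list of data used to find factors that affect adherence. Keep it as an adherence measure.
2. Name the adherence measure or measures used as the dependent variable. If several sources are used, fit a separate model for each and keep the existing definition of video adherence.
3. State that MARS is not a predictor in any model of factors explaining adherence.
4. If prior adherence is wanted as a covariate for video adherence during DOT, use only a MARS score from before DOT, in a separately labelled sensitivity model.
5. Take quality-of-life and ACT/C-ACT predictors from a visit before DOT starts: week 0 in the immediate group, week 0 or week 6 in the delayed group. State which.

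The cost is a few sentences. No new data or visits are needed, and the sample size does not change. Each explanatory model has one predictor fewer, which helps with 72 children.
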